#### Trial organization

The steering committee is composed of principal investigators who contributed to the design and approval of the final protocol (Additional file 2). The Executive Committee is composed of the main investigators and is responsible for the administration, trial, and data collection. The data management team is composed of external independent experts in anesthesiology, statistics, and imaging. It is responsible for checking the integrity and reliability of the data, and it will recommend the continuation or discontinuation of the trial according to the results of the interim analysis. The trial overseeing group is composed of a project manager and experts in methodology and ethics. It is responsible for monitoring recruitment rate, clinical intervention, and follow-up and arranging a research progress meeting with principal investigators every month.

## Discussion

This study is a single-center randomized controlled trial to determine if the pulmonary impedance-guided individualized PEEP during the period from dura suturing to extubation reduces the incidence and severity score of pulmonary complications within 1 week following a craniotomy compared with a single PEEP. Considering the effects of anesthesia duration, age, insulin-dependent diabetes mellitus, and chronic obstructive pulmonary disease on PPCs [28], all patients will have a BMI ranging from 18.5 to 28 kg/m^2^, are 18~65 years of age without diabetes, and have co-existing lung diseases to avoid the effect of these factors on outcome. PPCs are defined as clinically relevant and identifiable lung changes that adversely affect the prognosis of patients. Because this definition lacks accuracy in the diagnosis of PPCs, the reported incidence of PPCs varies considerably [29]. Some researchers regard the comprehensive results of multiple lung diseases as lung complications, and others regard a specific lung disease or respiratory condition requiring special treatment postoperatively as lung complications [30, 31]. In this study, the improved PPCs score table will be used as the standard to evaluate the incidence of PPCs after surgery. The PPCs will be evaluated from multiple perspectives, such as symptoms, signs, blood gas analysis, and imaging changes, so that the evaluation is more systematic and comprehensive, and the severity of pulmonary complications can also be graded.

PEEP has been used clinically for more than 30 years because PEEP can prevent alveolar collapse, improve functional residual capacity, and improve lung dispersion and compliance [32–34]. Sreejit et al. [35] reported that the application of PEEP during mechanical ventilation under general anesthesia can effectively prevent alveolar collapse and expand the collapsed alveoli, thus improving hypoxemia; however, due to individual differences between patients, standardized and fixed PEEP cannot be applied to all patients. There is still controversy regarding the optimal level of PEEP during surgery [36, 37]. Franchineau et al. [38] conducted a study on individualized PEEP on 15 patients requiring extracorporeal membrane oxygenation, and the results showed that PEEP varies greatly among different patients, which suggested the necessity of individualized PEEP.

EIT-guided PEEP titration is a PEEP titration strategy that has attracted much attention in recent years. EIT images show the percentage of collapse and overexpanded areas corresponding to different PEEP levels in the total ventilation area, from which a curve of the percentage of collapse and overexpanded area can be drawn. The PEEP corresponding to the intersection of the two curves facilitates alveolar re-expansion as much as possible, while minimizing overexpansion, and thus, it is determined as the best PEEP. In the pre-experiments, the median PEEP obtained by EIT was 6 cmH_2_O. Therefore, we compare Pi with P6.

Considering that PEEP may increase thoracic pressure, affect hemodynamic stability, further increase intracranial pressure, affect cerebral perfusion, and have an impact on rScO_2_, we have chosen to apply PEEP for mechanical ventilation from the beginning of dura suturing to the end of the surgical procedure and before extubation to avoid its impact on the key stage of surgery. The doses of vasoactive drugs, PaO_2_/FiO_2_, and regional brain oxygen saturation will be used as observation indices to clarify the effectiveness and safety of individualized PEEP. Studies have shown that in patients with severe and acute brain injuries, the application of PEEP has no effect on intracranial pressure (ICP) or cerebral perfusion pressure (CPP) for those without severe lung injuries [39]. The increase in intracranial pressure is modest over the range of applied PEEP values (0–25 cmH_2_O), suggesting that PEEP may be safely applied to most mechanically ventilated patients with severe brain injuries. Therefore, we believe that it is relatively safe to titrate individualized PEEP in the range of 0–10 cmH_2_O. The purpose of this study is to explore the application value of pulmonary electrical impedance-guided individualized PEEP in reducing pulmonary complications within 1 week after a craniotomy. If it can be demonstrated that individualized PEEP reduces the incidence and severity score of pulmonary complications within 1 week after a craniotomy, showing a statistical difference or clinical significance, the study will promote the wide application of individualized PEEP in clinical anesthesia, further improve the prognosis of neurosurgical patients, and reduce the cost of hospitalization.

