
Based on the different options for lung protective ventilation during operation, the patients will be randomly allocated into two groups (P6 or Pi groups). In order to avoid the influence of PEEP on cerebral blood flow and intracranial pressure and thus affect the exposure of surgical field, PEEP (PEEP = 0 cmH_2_O) will not be used in both groups during the period from tracheal intubation to dura mater suturing. At the beginning of dura suturing, patients in both groups will undergo a lung recruitment maneuver. The airway pressure will be maintained at 30 cmH_2_O for 30 s [23], then the PEEP will be increased from 0 to 10 cmH_2_O in a 2-cmH_2_O gradient, and each gradient will be maintained for 1 min [24]. After the lung recruitment maneuver, 6 cmH_2_O PEEP will be used in the P6 group and EIT-guided individualized PEEP will be used in the Pi group until the endotracheal tube is removed. In the pre-test, the median of the best PEEP is 6 cmH_2_O, so we plan to compare individualized PEEP with a single PEEP ( PEEP = 6 cmH_2_O ). The EIT-guided individualized PEEP titration method is as follows [19]: all patients will wear an EIT (PV500, Dräger, Germany) electrode belt (including 16 electrodes) before anesthesia. During the increase in PEEP from 0 to 10 cmH_2_O, the data of pulmonary electrical impedance at each PEEP will be obtained. The EIT Data Analysis Tool (6.1) will be used to analyze the insufficient ventilation and excessive expansion areas at different PEEP and plot a graph (Fig. 2). EIT-guided individualized PEEP is considered as the nearest PEEP above the crossing of the curves representing overdistension and collapse.

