The secondary outcomes of this study are as follows:Severity of pulmonary complications within 1 week: The severity of pulmonary complications will be assessed daily, until 1 week after surgery, using the worst score within a week for analysis. The modified PPC scoring table will be scored on an ordinal scale ranging from 0 to 5, in which grade 0 represents no pulmonary complications, grades 1–4 represent gradually deteriorating pulmonary complications, and grade 5 represents death of patients caused by respiratory diseases before discharge (Table 2).LUS: Lung ultrasound examination will be performed using the 2−5-MHz convex array ultrasonic probe of Edge (Sonosite Corporation, USA) before anesthesia (T0), 10 min after extubation (T1), 24 h after extubation (T2), and 72 h after extubation (T3). Twelve lung regions will be examined [26]; the lung on each side is divided into two areas by the fourth intercostal space: the upper and lower lung areas, and the upper and lower lung areas of the right and left lungs are delineated by the parasternal, anterior axillary, posterior axillary, and paravertebral lines. Therefore, both lungs are divided into 12 areas according to body surface markers. According to the improved scoring table (Table 3), the highest LUS of each lung area is 3 points and the lowest LUS is 0 points. Therefore, the total score of LUS ranges from 0 to 36 points. The higher the LUS, the more severe the atelectasis in this area [27].Regional cerebral oxygen saturation (rScO_2_): The 5100C brain and regional blood oxygen detection system (Covidien Corporation, USA) will be used to monitor rScO_2_ at T0, T1, T2, and T3. The mean value of the bilateral rScO_2_ will be considered as the rScO_2_. To ensure the accuracy of data, rScO_2_ will be collected 3 times, with an interval of 10 s each time, and the average value of the 3 values will be calculated.Arterial oxygen partial pressure/inspired oxygen fraction (PaO_2_/FiO_2_): arterial blood will be collected at T0, T1, T2, and T3 for blood gas analysis to determine the PaO_2_/FiO_2_.Postoperative ICU and hospital stays.Other research indicators include the duration of surgery and anesthesia, level and duration of PEEP, blood loss volume, blood transfusion volume, fluid input and urine output during surgery, and dosage of anesthetics and ephedrine during surgery (Table 4).

**Table 3 Tab3:** Scoring criteria for lung ultrasound images

Score	Ultrasonic image

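### No rScO2 or PaO2/FiO2 reading falls while PEEP is applied, so these two safety indices can show only after-effects; the whole-surgery ephedrine total is unbiased but diluted

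*Protocol article*

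**What the plan says.** **Purpose.** The Discussion gives the worry directly: "PEEP may increase thoracic pressure, affect hemodynamic stability, further increase intracranial pressure, affect cerebral perfusion, and have an impact on rScO_2". It then names vasoactive drug doses, PaO2/FiO2 and rScO2 together as the indices of benefit and safety: "regional brain oxygen saturation will be used as observation indices to clarify the effectiveness and safety of individualized PEEP".

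**Exposure.** Under Related parameter setting during operation, PEEP "will not be used in both groups during the period from tracheal intubation to dura mater suturing". Both arms then have a recruitment maneuver with stepwise PEEP. After it, each arm stays on its assigned PEEP until the tube is removed.

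**Measurement.** Under Primary and secondary outcomes, the cerebral oximeter "will be used to monitor rScO_2_ at T0, T1, T2, and T3", and "arterial blood will be collected at T0, T1, T2, and T3 for blood gas analysis". The time points are defined as "before anesthesia (T0), 10 min after extubation (T1), 24 h after extubation (T2), and 72 h after extubation (T3". The Abstract and the Introduction give the same times. Among the other research indicators is "dosage of anesthetics and ephedrine during surgery", which has a single ephedrine row in Table 4.

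**The concern.** The effects on thoracic pressure, intracranial pressure and cerebral perfusion that the Discussion describes would arise while PEEP is on. Two of the three named indices are never read then. Equal rScO2 in the two arms 10 minutes after extubation is compatible both with no cerebral effect of PEEP and with an effect that ended when PEEP ended. Read against the Discussion, such a result could be taken as evidence of safety during exposure, which it is not. No later analysis can recover readings that were never taken.

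The contrast is not empty. Titration runs over 0 to 10 cmH2O and the pre-test median was 6 cmH2O, so individual patients in the Pi group may be above or below the control level.

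The third index, ephedrine, does cover the exposure period but adds it to an earlier period in which the arms do not differ. Random variation from that earlier period makes a difference caused by PEEP harder to see.

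**Working it through.** **1. Reading times against the PEEP window**

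The window opens at dura suturing and closes at extubation.

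| Reading | Time | PEEP on? |
|---|---|---|
| T0 | before anesthesia | no, not yet intubated |
| T1 | 10 minutes after extubation | no, PEEP has ended |
| T2 | 24 hours after extubation | no |
| T3 | 72 hours after extubation | no |

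Result: 0 of 4 for rScO2 and, on the same schedule, 0 of 4 for PaO2/FiO2.

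**2. Ephedrine: bias**

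Write the total as T = A + B, where A is the dose from intubation to dura suturing and B the dose from dura suturing to extubation. Both arms have zero PEEP during A, so randomization gives E(A | Pi) − E(A | P6) = 0. The arm difference in T therefore has the same expectation as the arm difference in B. This takes the recorded period to run to extubation, which the text does not spell out. It also takes the anesthesiologist, who knows the allocation, to treat the arms alike before dura suturing.

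**3. Ephedrine: precision**

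Let f = Var(B) / Var(T), with A and B independent. The standard error of the arm difference is then SD(T)/SD(B) = 1/√f times larger for T than for B, and the sample size needed is 1/f times larger. The document gives neither phase durations nor dose timing, so f is unknown. The values below are assumptions.

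The arm size for the illustration is the plan's own 216, which reproduces. With rates 0.24 and 0.135, mean 0.1875, two-sided alpha 0.05 and power 0.80:

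n = [1.96 √(2 × 0.1875 × 0.8125) + 0.842 √(0.24 × 0.76 + 0.135 × 0.865)]² / 0.105² = 215.7, rounded up to 216. Allowing for 20% dropout, 216 / 0.8 = 270.

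Assume also a true difference of 0.3 SD of B. Power is then Φ(0.3 √f √(216/2) − 1.96). Analysing B alone (f = 1) gives Φ(3.118 − 1.96) = 88%. For the total:

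| f (assumed) | SE ratio 1/√f | Sample size multiple 1/f | Power using the total |
|---|---|---|---|
| 0.5 | 1.41 | 2.0 | 60% |
| 0.3 | 1.83 | 3.3 | 40% |
| 0.2 | 2.24 | 5.0 | 29% |
| 0.1 | 3.16 | 10.0 | 17% |

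The table shows the direction and how strongly the loss depends on f. It does not estimate the loss in this trial.

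**The case against.** The strongest case on the other side has four parts.

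- **The safety question is wider than rScO2.** Adverse events are recorded with severity and causality (Reporting of adverse events). Severe brain swelling during surgery and persistent hypotension with circulatory instability are withdrawal conditions (Sample size estimation and interim analysis). Arterial pressure is monitored invasively. This stands. A reader might infer that the safety question cannot be answered at all, and the document does not support that: overt events during exposure are captured, and the ephedrine total is a valid randomized comparison. What remains uncovered is cerebral oxygenation on PEEP.
- **After-effects are a safety question too.** The Discussion does not say that rScO2 is meant to show the acute effect alone. This also stands, and T1 to T3 keep their value. But the sentence just before speaks of what PEEP does to pressure and perfusion, and the readings cannot address that.
- **Ephedrine timing may be in the full protocol.** Table 4 is a reporting shell, and an article may leave phase-specific recording to the full document. This is fair, and it makes ephedrine the lesser part of the point. A reader might also infer that most ephedrine is given in the zero-PEEP phase; the document gives no figure for this.
- **The schedule figure is not available here.** That is so, but the text gives the same reading times in three places and mentions no intraoperative rScO2 reading.

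The comparison is also limited by design. Both arms receive recruitment and PEEP, so no index can speak to PEEP versus none.

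**Conclusion.** The point holds for rScO2 and PaO2/FiO2. Both are named as safety indices and have 0 of 4 readings during exposure. This rests on the document's own times and needs no assumption. As scheduled, they can support a statement about effects after extubation of individualized PEEP versus 6 cmH2O, and nothing about cerebral oxygenation while PEEP is on.

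For ephedrine the point is one of sensitivity. The total is unbiased for the same contrast, with a standard error larger by 1/√f if the two phases are independent. The size of f cannot be taken from the document.

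The primary outcome, the sample size and the primary comparison are untouched.

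**What to change.** 1. **rScO2.** With the monitor already in use, take a reading just before the recruitment maneuver and another on the assigned PEEP, in remaining patients where the sensor site allows. Compare arms on the on-PEEP reading, adjusted for the pre-recruitment reading. The arms are treated alike up to that first reading, so adjusting for it is sound.
2. **If on-PEEP readings are not feasible,** limit the Discussion's safety statement for rScO2 to post-extubation effects of individualized PEEP versus 6 cmH2O. For PaO2/FiO2 this limit is needed in either case, since no new blood sample is proposed.
3. **Ephedrine.** Take the dose given from dura suturing to extubation from the anesthesia record and compare arms on that. The whole-surgery total can still be reported.

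**Cost.** A few extra readings per patient and one more field from an existing record. Recruitment began on 1 September 2021 and was under way at publication, so the new rScO2 readings will be missing for patients already treated. They will also be missing for some frontal approaches where the sensor cannot stay in place. The on-PEEP comparison would therefore rest on a subset and should be reported as such. Option 2 costs only a change of wording.

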### Trial status

The study was registered on the registry website http://chictr.org.cn/ with registration number CHiCTR2100051200 on 15 September 2021. The protocol version is 1.0, dated 20 September 2021. The study began on 1 September 2021, and the planned completion date will be 30 September 2023. The trial status is currently recruiting. Recruitment began on 1 September 2021, and the planned recruitment completion date will be June 2023.

## Data Availability

The full protocol and datasets analyzed during the current study are available from the corresponding author upon reasonable request.

## Abbreviations

EIT: Electrical impedance tomography
PEEP: Positive end-expiratory pressure
LUS: Lung ultrasound score
PPCs: Postoperative pulmonary complications
PLV: Protective lung ventilation
ARM: Alveolar recruitment maneuver
ICP: Intracranial pressure
rSO_2_: Regional cerebral oxygen saturation
PaO_2_: Partial pressure of oxygen
FiO_2_: Fraction of inspiration oxygen
BMI: Body mass index
ECG: Electrocardiogram
ETCO_2_: End-expiratory carbon dioxide
BIS: Bispectral index
MAP: Mean arterial pressure
PaCO_2_: Partial pressure of carbon dioxide
SpO_2_: Pulse oxygen saturation
ICP: Intracranial pressure
CPP: Cerebral perfusion pressure
VT: Tidal volume
